High-density genotyping of common polymorphism (minor allele frequency > 1%) will be performed using Illumina BeadChip microarrays. Genotypes will be used to control for ancestry and relatedness in the cohort, and quality-controlled genotypes will be formatted for association analyses with phenotypes collected.

- 1. Option for study staff to have access to genetic data for future study recruitment.

Genetic confirmation of DM1 is not required for entry in the study. The clinical diagnosis of DM1 is > 99% accurate. Since CTG repeat number does not have an established prognostic value, the current standard of care does not require genetic testing. Accordingly, most DM1-affected individuals in the U.S. have not had genetic testing. For example, 50% of patients in the National Registry of Myotonic Dystrophy (*n* = 947) have not had genetic confirmation. This creates a potential barrier for participation in research studies.

Genetic testing for CTG expansion at the DM1 locus will be performed on all participants in the study. The testing will be performed in a research laboratory, not a CLIA-certified genetic testing laboratory. The test results will not be provided to participants.

Participants in the study will have the option for *DMPK* genetic test results to be placed in the local study binder for future access by site investigators and study staff. For participants who make this selection, the study site staff have the option to reference DM1 genetic test results for future study recruitment. Participants will indicate their selection by checking a box on the consent form. Note that study binders are the only place where DNA test results and personal identifiers are linked. Contact with participants for future studies is exclusively done by sites, and cannot be performed from the central Coordinating Center, which will never have access to patient identifiers (see below). Our goal in providing this option is to eliminate genetic diagnosis as a barrier to participation in research studies.

All participants in the study will have a clinical or genetic diagnosis of DM1. Accordingly, the results of DM1 genetic testing are not expected to impact patient care. In the unlikely event that CTG expansion is not confirmed, the participant may instead have myotonic dystrophy type 2 (caused by repeat expansion in a different gene) or a type of myotonic dystrophy that is not yet described. If this occurs, the subject will be notified and offered arrangements for further neuromuscular evaluation and genetic counseling.

- 1. BioBank of muscle tissue and blood.

Participants in the study will provide their consent for muscle tissue, blood, and urine to be placed in a BioBank. Materials in the BioBank may be used for future unspecified research by investigators within or outside of the Myotonic Dystrophy Clinical Research Network. Materials in the BioBank will include muscle tissue, blood, and urine, and DNA, RNA, or protein derived from these samples. The creation of the BioBank does not imply a commitment to fulfill all requests for research materials, because the quantities of tissue and RNA from needle biopsy samples are limited. BioBank samples will be stored in Drs. [name] or [name]’s laboratories in barcoded tubes. When samples are provided to investigators, they can be accompanied by de-identified study data, including age, gender, and indices of disease severity (e.g., muscle strength, timed functional test scores, myotonia scores, MDHI scores). There is no mechanism for laboratory investigators to trace a sample back to individual study participants. The entire sample will be allocated to the BioBank. The first priority for sample analysis is the analysis described in this protocol. Samples that remain can be used for future unspecified research, including proteomic or transcriptomic analyses. Samples distributed to other scientists will not be returned.

- 1. **Safety Assessments**

Assessments that will be performed to evaluate safety are: medical history, physical exam, vital signs, and EKG.

- 1. **Data & Specimen Banking for Future Research Use**

By participating in this study the patient agrees that remaining samples of their muscle tissue, blood, and urine may be kept indefinitely in the Myotonic Dystrophy BioBank at the University of Rochester and University of Utah. The samples may include muscle tissue, blood, urine, or materials derived from these samples, such as protein, RNA, DNA, and cells. The samples will be identified by a code number; not by the patient’s name or other identifying information. The details about future research cannot be described at this time because they depend on scientific advances in the field. The future research may be carried out by qualified scientists in the Myotonic Dystrophy Clinical Research Network or at other facilities. Future researchers who use BioBank samples may be provided with de-identified information about how the patient is affected by DM1, such as muscle strength or walking speed. Researchers will not be provided with information that can directly identify you. Researchers using the samples will be asked to acknowledge the BioBank when they announce results of their studies. However, the patient will not be able to determine whether their samples were used in a particular study, and the patient will not be notified when their samples are provided to researchers. The patient will not benefit financially from potential new discoveries or technological advances brought about through research using samples from the BioBank. The study staff may decide to stop storing materials in the BioBank without sending the patient notice or obtaining their permission.

As part of the BioBank the patient also has the option to allow a cell line to be made from their blood to provide a renewable supply of DNA and other cell components for research. A cell line is a frozen sample of specially processed cells from the patient’s blood that allows researchers to grow more cells and obtain more DNA and other cell components, such as RNA or proteins, for future research. The cell line would not be labeled with the patient’s name, address, birthdate, or other personal identifiers. It is possible that the patient’s cell line would be used in the future by the University of Rochester or research partners for testing or developing a treatment or commercial product. There are no plans to provide financial compensation to the patient should this occur. Patients have the option to check the box in the consent giving permission for have a cell line made from their blood for future research.

- 1. **Genetic/Genomic Research Activities**

Part of the patient’s blood sample will be used for genetic testing. If the patient does not understand what a genetic test is and wishes to receive genetic counseling prior to signing this consent form, they can let the investigator or coordinator know.

The patient’s blood sample will be labeled with an identification code number. The coded sample will be sent to researchers at the University of Utah for isolation of DNA, the genetic material. The patient’s name, address, birth date, and other personal information will not be included with the sample. The researchers at University of Utah or at another site will test the DNA for the gene abnormality that causes DM1. The test will be performed in a research laboratory, not in a certified medical testing laboratory, therefore the results will not be provided to the patient. The patient will have the option for study staff at the University of Rochester to keep their DM1 genetic test results on file for up to eight years. This may eliminate the need for repeat genetic testing in future studies, and the results may be used to identify people who are eligible to take part in future studies. The patient has the option to check the box in the consent form giving study staff at the University of Rochester permission to store their DM1 genetic test result and contact the patient about participation in future studies.

Another part of the patient’s DNA sample will be used by researchers at the University of Utah or another site to test for DNA variants (differences) that are known to occur in human genes. The researchers will be searching for variants that determine how people are affected by DM1. This is an important question because the effects of DM1 are very different from one person to the next. The researchers will receive de-identified information about how the patient is affected, such as their muscle strength, walking speed, and questionnaires. This information will not include the patient’s name, birthdate, address, or other personal identifiers. The information will be matched to the code number of their DNA sample. If researchers are successful in discovering gene variants that affect DM1, the study staff at the University of Rochester may contact the patient in the future to ask about participation in additional studies. Patients have the option to check the box in the consent form giving study staff at the University of Rochester permission to contact the patient about participation in future studies to learn more about DNA (genetic) variants that affect DM1.

- 1. **Costs to the Subject**

There is no cost to research patients to participate in this research study.

- 1. **Payment for Participation**

Patients will be provided an honorarium of $150 for each of the needle muscle biopsies, for a total of $300.

- 1. **Return of Individual Research Results**

The genetic testing will be performed in a research laboratory, not in a certified medical testing laboratory, therefore the results will not be provided to the patient.

1. **CONCOMITANT AND DISALLOWED MEDICATIONS**

Not applicable

1. **SUBJECT WITHDRAWALS**

Possible reasons for withdrawal may include loss of funding, completion of the study, if the patient misses their study visits, or a concern by study staff that participation may have a harmful effect on the patient’s emotional or physical health or welfare.

1. **SAFETY AND REPORTABLE EVENTS**
   1. **Definition of an Adverse Event and Medical Event**

For this study, an *adverse event* is any new, undesirable medical occurrence or change of an existing condition in a subject that occurs during a study visit. An adverse event could be a fall during a 6 minute walk test, a complication during a needle muscle biopsy, etc. We will not capture changes that are occurring as part of the disease progression as an adverse event. These changes will be captured under the Medical History CRF (06) and updated at each visit.

For this study, a *medical event* is any change in symptom, change in frequency, new diagnosis, sickness, hospitalization, surgeries, etc. that happen within the 12 month period that the patient is enrolled in the study. These items will be documented on the Medical History Form (06).

- 1. **Adverse Event and Medical Event Reporting Period**

The recording of adverse events will begin with the start of protocol-specific procedures. Reporting will continue until the last in-person study visit or when a subject ends participation in the study.

- 1. **Reviewing Adverse Events and Medical Events**

Inquiries about medical events will occur at every visit. In addition, subjects will be instructed to contact the study coordinator about any concerns or changes in health status.

Adverse events will be reviewed by with the site investigator and study coordinator at each study visit.

- 1. **Adverse Event and Medical Event Coding**

Coordinators will list a complete description of the adverse/medical event including area of body affected and symptoms. The NMD-CC will code adverse events at the time of data analysis.

- 1. **Adverse Event Follow-up**

The site investigator will review all ongoing adverse events with the subject during each visit and telephone call to evaluate any change in status. All adverse events will be monitored by the treating neurologist until resolution or the end of the study’s AE reporting period. Resolution of an adverse event is defined as a return to the subject’s baseline condition (level of symptoms, laboratory value or frequency of episodes).

The progress of each SAE will be followed by the study PI until resolution or until an appropriate endpoint is reached. An appropriate end point is the resolution of the event or the determination that the event has become chronic or stabilized.

- 1. **Required Reporting Elements**

Details regarding adverse events will initially be entered in the subject’s progress notes as source documentation. Each adverse event will be recorded on the subject’s Adverse Event Log (CRF 56). All of the required data elements included on the Adverse Event Log must be completed for each event. A description of each item required on the Adverse Event Log is described in sections 2.1a – 2.1h.

8.6.a **Adverse Event Description**

Capture a complete description of the adverse event including the area of the body affected as well as symptoms experienced by the patient.

8.6.b **Record Date**

The date an event is recorded is the day that study staff becomes aware of the adverse event either during a study visit, phone call or through the receipt of test results. A complete date must be entered for this field on the Adverse Event Log.

8.6.c **Severity**

The site investigator or study coordinator will grade the severity of each adverse event using the detailed clinical descriptions provided below. This grade will be entered in the appropriate field on the Adverse Event Log.

The general guidelines for grading each adverse event are based on the following scale:

| **Grade** | **Description** |
| --- | --- |
| 1 | Mild; Asymptomatic or mild symptoms; clinical or diagnostic observations only; intervention not indicated. |
| 2 | Moderate; minimal, local or noninvasive intervention indicated; limiting age-appropriate instrumental ADL |
| 3 | Severe or medically significant but not immediately life-threatening; hospitalization or prolongation of hospitalization indicated; disabling; limiting self care ADL |
| 4 | Life-threatening consequences; urgent intervention indicated. |
| 5 | Death related to AE. |

A semi-colon reads as the word ‘or’ within the description of the adverse event’s grade.

8.6.d **Action Taken**

The actions taken to manage adverse events must be recorded using the terms listed in the table below. A minimum of one term must be entered for each adverse event. Multiple actions can be entered.

- None
- Hospitalization
- Terminated from the study
- Unknown
- Medication
  Other

Any changes in concomitant medication must be recorded on the Concomitant Medication Log (CRF26).

The term “Hospitalization” refers only to inpatient hospitalization. “Hospitalization” should not be recorded if a subject was admitted as an outpatient for a procedure. Outpatient procedures can be documented as a response to an adverse event using the code “Other.” The subject’s source documentation will capture information about the procedure.

8.6.e **Seriousness**

The site investigator will evaluate if the adverse event meets the criteria for being a Serious Adverse Event. A Serious Adverse Event (SAE) is defined as any adverse event that:

- Results in death
- Is life-threatening or places the participant at immediate risk of death from the event
- Requires inpatient hospitalization or prolongation of existing hospitalization. Hospitalizations scheduled before enrollment for an elective procedure or treatment of a pre-existing condition which has not worsened during participation in the study will not be considered a serious adverse event.
- Causes persistent or significant disability/incapacity (substantial disruption of one's ability to conduct normal life functions) that is not related to the underlying myotonic dystrophy
- Results in a congenital anomaly/birth defect
- Is a medically important event that required medical intervention to avoid one of the above outcomes

If an AE meets the criteria for being serious, the AE must be listed on the primary Adverse Event Log (CRF56) and additional information must be submitted using the Serious Adverse Event Form (CRF57). Additional instructions on reporting Serious Adverse Events are located in section 3.0.

8.6.f **Outcome**

Resolution of an adverse event is defined as a return to the subject’s baseline condition (level of symptoms, laboratory value or frequency of episodes). Otherwise, mark the outcome as “ongoing.”

8.6.g **Start Date**

The start date is the day an adverse event begins

If study personnel are unable to determine an exact date based on the subject’s report or available records, the study personnel must estimate a start date using the information available. Additional details for entering dates are included in the study manual section, Data Collection and Documentation.

8.6.h **End Date**

The end date is the day an adverse event resolves or the subject returns to their baseline condition.

If study personnel are unable to determine an exact date based on the subject’s report or available records, the study personnel must estimate an end date using the information available.

At the end of the study, any adverse events that have not resolved will be recorded as “ongoing” on the Adverse Event Log (CRF56).

An end date will only be entered for adverse events that have resolved. Resolution of an adverse event is defined as a return to the subject’s baseline condition.

8.6.i **Neurologist Review**

The site investigator will review the Adverse Event Log (CRF56) after each visit to ensure that all adverse events have been entered correctly.

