Approximately 500 adult patients (18 to 70 years old, inclusive) with DM1 will be enrolled at 9 centers (up to 56 patients will be recruited at each site). No treatment will be administered as part of this study. Patients will receive standard of care as determined by their treating physician. Study visits occur at baseline/0 months, 12 months, and 24 months. Few restrictions are placed on participation in the study because we aim to capture the full spectrum of disease severity. Studies of splicing biomarkers in muscle biopsy samples will be conducted on a subset of 60 participants. These patients will have an additional study visit at 3 months.

1. **CHARACTERISTICS OF THE RESEARCH POPULATION**
   1. **Subject Characteristics**
2. **Number of Subjects:** This study will enroll 500 DM1 participants across 9 sites and 56 subjects will enroll locally at the University of Rochester.
3. **Gender and Age of Subjects:** DM1 has a prevalence rate of approximately 1 per 7,500. There are no expected gender differences. Both men and women will be selected for this study.

Children with DM1 are not included in this project because the pathophysiological basis of congenital and childhood DM1 appears to be mechanistically distinct.

1. **Racial and Ethnic Origin:** Prevalence rates of DM1 in major ethnic populations are not documented within the U.S. However, DM-1 prevalence rates in Africa are much lower than those in Europe and the US1. The demographics of myotonic dystrophy in Monroe County are not known. However, the latest demographics of Monroe County (White 77.0%, Black 16.2%, Hispanic 8.5%, Asian 3.7%, Native American 0.1%) indicate that our area contains minority populations similar to the national distribution (https://www.census.gov/quickfacts/fact/table/monroecountynewyork/PST045216). We have based our recruitment projections to reflect the demographics of Monroe County which closely parallel those of the general U.S. population.

The relative gender and minority balance in the Registry will enable us to more quickly and easily recruit patients to the University of Rochester.

- 1. **Inclusion and Exclusion Criteria**

1. **Inclusion Criteria:**

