*One Back Test.* This is a test of working memory that uses an n-back paradigm. A playing card is presented to the participant facing up in the center of a screen. The participant must decide if the presenting card is identical to the previously presented card. Participants are asked to respond “Yes” or “No” accordingly. There is a practice period followed by the actual test. Participants are encouraged to work as quickly and as accurately as possible. Speed of performance is measured and reaction times are transformed for correct responses. A lower score indicates better performance.

*Identification Test.* This test measures attention by utilizing a choice reaction time paradigm. A card is flipped over face up. The participant must decide whether the card is red or not. If red, he/she presses the “Yes” key, and if not, he/she presses the “No” key. Participants are encouraged to press the appropriate key as quickly and as accurately as possible before the card flips over. Performance speed is measured. A lower score indicates better performance.

*Social-Emotional Cognition Test.* For this test, emotional recognition is measured using an odd-man–out paradigm. Participants are presented with a number of pictures on screen. One of the pictures is different in some way, and the participant must decide which image is different and tap it. Participants are encouraged to work as quickly and as accurately as possible. Accuracy of performance is measured. A higher score indicates better performance.

- 1. Biomarkers and muscle biopsy substudy

*Blood sample*. A blood sample will be collected at each visit to obtain plasma samples for biomarker discovery. The sample may be used to assess plasma RNA, metabolites, or proteins.

Blood tubes to be collected:

- *Yellow top* (8-10 ml) for DNA at baseline, 12 month, and 24 month study visits.
- *PAXgene tube* (2 tubes, 2.5 ml each tube, total 5 ml) for blood RNA at all three visits
- *Yellow top #2* (8-10 ml) for plasma at all three visits

Sample Processing:

*Yellow top* *for DNA.* The preferred method is that samples are placed in a -80 C freezer within two hours of collection. Samples may then be batch shipped to the University of Utah on dry ice. Alternatively, samples may be stored at 4 C for up to two days and then shipped overnight to the University of Utah.

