*PAXgene tube*. Once collected, samples need to remain at room temperature for 2 hours. After this, samples may be stored in a -80 C freezer and then batch shipped to the University of Utah on dry ice.

*Yellow top #2*. Samples should be centrifuged for 10 minutes at 4000 RPM at 4 C immediately after collection. The supernatant (plasma) should be aspirated, divided into 3 aliquots, and stored in new tubes. The samples should be placed at -80 C immediately, then batch shipped to the University of Utah on dry ice.

*Urine sample.* The urine sample will be divided in two 5 ml tubes and stored at -80 C for batch shipping.

*Electrocardiogram (ECG).* This will be performed at each visit to evaluate the extent of cardiac conduction disease. PR interval and QRS duration will be determined using standard methods.

*Muscle biopsy sub-study*. The biopsy sub-study will examine RNA splicing defects that are characteristic of DM1. The proposed study builds on results from the initial DMCRN study, in which we obtained paired needle biopsy samples of tibialis anterior muscle from 97 patients. The samples were obtained 3 months apart to approximate the expected time course of muscle sampling in early-phase clinical trials. No significant safety issues were encountered. The biopsy procedure was well tolerated and > 95% of subjects who underwent the initial biopsy returned for the second biopsy. The second biopsy was obtained from the same leg, except in 19 patients whose second biopsy was obtained from the opposite leg. RNAseq of biopsy samples has now been completed and the preliminary analyses indicate that test-retest reliability of splicing biomarkers was substantially better for paired samples obtained from opposite legs. We seek now to confirm this finding in an independent cohort. Furthermore, in discussions with FDA officials about splicing biomarkers, the question was raised whether RNA splicing defects observed in tibialis anterior are representative of other muscles. Therefore, we are also testing whether splicing misregulation in an arm muscle, biceps brachii, is similar to that in tibialis anterior.

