**8.13 SAE Follow-up Reports**

The site investigator must provide any updated information about the SAE during the reporting period until the event has resolved or stabilizes. Any new pertinent information on an SAE obtained after the initial submission of the SAE Form (CRF 57) will be recorded on the SAE Follow up Form (CRF 58).

1. The SAE Follow-up Form (CRF58) will be completed by the site investigator or study coordinator. The site will include deidentified copies of any new relevant medical records such as a discharge summary, hospital notes and laboratory results.

2. The site will send a copy of the SAE Follow-up Form (CRF58) and other documentation to the PI and NMD-CC project coordinator. The documents can be sent as a fax or emailed as a PDF attachment. The NMD-CC SAE Follow-up fax cover sheet should be used when sending these documents. This form is included in the Appendix of the Study Manual.

3. The study PI will review the information that was submitted. Additional SAE Review Forms (CRF59) will be completed by the study PI if:

- - - - The classification of the event changes (relatedness or expectedness)
      - The event has resolved or an appropriate endpoint has been reach (resolution or determination of the event to be chronic and/or stabilized)

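### The plasma spin is fixed as a rotor speed (4000 RPM) and not as a centrifugal force, so plasma processing may differ between the 9 sites

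*Protocol*

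**What the plan says.** The rule is in the Protocol under Methods and Study Procedures, Biomarkers and muscle biopsy substudy, in the processing steps for the second yellow-top tube: "Samples should be centrifuged for 10 minutes at 4000 RPM at 4 C immediately after collection". The supernatant is then aliquoted, and the next step reads: "The samples should be placed at -80 C immediately, then batch shipped to the University of Utah on dry ice". The spin is therefore done at the collecting site, before anything reaches the central laboratory.

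The same section gives the purpose: "A blood sample will be collected at each visit to obtain plasma samples for biomarker discovery". On the assays it is permissive: "The sample may be used to assess plasma RNA, metabolites, or proteins". The tube list has this tube drawn "for plasma at all three visits", that is at baseline, 12 and 24 months. Under Rationale for Study Design, about 500 patients "will be enrolled at 9 centers".

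No force in x g, rotor radius or centrifuge model appears anywhere in the protocol. The DNA and PAXgene tubes have no spin step.

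**The concern.** RPM is a setting on a machine. What acts on the sample is the relative centrifugal force (RCF), which is proportional to rotor radius at a given speed. Force and time together govern how many cells and platelets stay in the supernatant. Because the aliquots are frozen straight away, whatever remains is frozen with the plasma. If rotors differ in radius, the plasma could carry a site-related difference that has nothing to do with the disease.

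At stake is the comparability across sites of plasma used for biomarker discovery, and of plasma kept for later use. The BioBank section allows future proteomic and transcriptomic work. The confidentiality section foresees an industry partner's scientists linking plasma to study data. The clinical data that the BioBank section names as examples to accompany samples are age, gender and severity indices. Site and rotor are not among those examples, so a later user might lack what is needed to adjust.

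**Working it through.** The plan has no calculated figure to reproduce; 4000 RPM is a setting. The check asks what force that setting produces.

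**Inputs**
- Speed 4000 RPM, 10 minutes, 4 C: plasma processing step.
- 9 sites, each spinning locally: Rationale for Study Design and the processing step.
- 500 participants, three plasma visits: study design and tube list.
- 10% dropout: Sample Size Determination.
- Rotor radius r: not given. Assumed for illustration, 8 to 20 cm.

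**Formula**

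RCF = (2 x pi x RPM / 60)^2 x r / 9.80665, with r in metres. This is the same as RCF = 1.118 x 10^-5 x r(cm) x RPM^2.

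At 4000 RPM: 1.118 x 10^-5 x 16,000,000 = about 179 x g per cm of radius.

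| Assumed radius (cm) | Force at 4000 RPM (x g) |
|---|---|
| 8 | 1,431 |
| 10 | 1,789 |
| 12 | 2,147 |
| 15 | 2,684 |
| 17 | 3,042 |
| 20 | 3,578 |

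At a fixed speed the ratio of forces between two sites equals the ratio of their radii:
- equal radii: 1.0
- 15 and 17 cm: 17/15 = 1.13
- 10 and 17 cm: 17/10 = 1.7
- 8 and 20 cm: 20/8 = 2.5

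**Samples covered.** At most 500 x 3 = 1,500 collections. If the 10% dropout all occurred between baseline and month 12, the number would be 500 + 450 + 450 = 1,400.

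**What the arithmetic settles.** A fixed RPM does not determine a force, whatever radii are assumed. It does not show that the forces at these nine sites differ, or by how much.

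**The case against.** The strongest case against raising this is that it is bench detail on exploratory samples, and that the protocol does not contradict itself: it fixes time, temperature, speed, aliquots and storage. A study manual exists. It is cited, for example, for a safety-reporting fax sheet ("This form is included in the Appendix of the Study Manual"), and it may name a rotor or a force. That manual is not at hand, so nobody can say that the study as run lacks this control. This part stands, and it limits the point to the protocol's own line. It does not remove the point: the protocol sets the value itself, and if the manual states a force the two should be aligned.

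A reader might also infer more than the protocol supports:
- **That the sites do process plasma differently.** No site's centrifuge or rotor is described. Equal radii give equal force.
- **That the spread is 2.5-fold.** That is the extreme of an assumed range; closer radii give 1.13 or 1.7.
- **That change from baseline to 24 months is distorted.** With an unchanged rotor the force is the same at each of a participant's visits. A spurious within-participant change from this source needs a switch to a rotor of different radius, and nothing in the protocol suggests one.
- **That site effects are mixed up with case mix.** The protocol gives a common recruitment cap per site and describes no site-specific population.
- **That the damage is beyond repair.** Residual cells cannot be removed after freezing. But if each site keeps one rotor, the effect is between sites, and adjustment for site can largely absorb it.

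**Conclusion.** The point holds as a gap in standardisation: the protocol specifies the plasma spin in a unit that does not fix the force, so processing may differ between sites that comply exactly. Under assumed radii the between-site ratio of forces lies anywhere from 1.0 to 2.5. The true value is unknown because the radii are unknown. The size of any effect on plasma RNA, metabolites or proteins cannot be derived from the protocol.

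The reach is narrow. Plasma work is optional and is not among the three stated purposes. The key endpoints (30-foot go, grip strength, ADF strength, supine FVC) do not use plasma. The splicing work uses frozen muscle, and genotyping and CTG sizing use DNA from a separate tube with no spin step. No conclusion on a stated purpose depends on this point. It is a minor improvement, worth making because it is nearly free and because the spin cannot be repeated once the plasma is frozen.

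**What to change.** Replace 4000 RPM with a single force in x g chosen by the sponsor's laboratory, for example the force that 4000 RPM gives on its reference rotor. Keep the stated time and temperature. Have each site convert to its own speed by RPM = sqrt(RCF / (1.118 x 10^-5 x r)), with r in cm, and record the RCF or rotor radius on the sample log.

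To show the conversion only, an arbitrary 2,000 x g would need about 4,728 RPM at 8 cm, 4,229 at 10 cm, 3,453 at 15 cm and 2,990 at 20 cm. This is not a proposed value.

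For plasma already banked, collect each site's rotor radius, with dates of any change of centrifuge, and adjust for site or RCF in plasma analyses. Make site or RCF available with samples released to other users. If the study manual already states a force, align the protocol line with it.

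Cost: one protocol line, one conversion per site and one log field. No new equipment is needed.
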